## Abstract

**Background:**

Fall-related hip fractures result in significant personal and societal consequences; importantly, up to half of older adults with hip fracture never regain their previous level of mobility. Strategies of follow-up care for older adults after fracture have improved investigation for osteoporosis; but managing bone health alone is not enough. Prevention of fractures requires management of both bone health and falls risk factors (including the contributing role of cognition, balance and continence) to improve outcomes.

**Methods/Design:**

This is a parallel group, pragmatic randomized controlled trial to test the effectiveness of a post-fracture clinic compared with usual care on mobility for older adults following their hospitalization for hip fracture. Participants randomized to the intervention will attend a fracture follow-up clinic where a geriatrician and physiotherapist will assess and manage their mobility and other health issues. Depending on needs identified at the clinical assessment, participants may receive individualized and group-based outpatient physiotherapy, and a home exercise program. Our primary objective is to assess the effectiveness of a novel post-discharge fracture management strategy on the mobility of older adults after hip fracture.

We will enrol 130 older adults (65 years+) who have sustained a hip fracture in the previous three months, and were admitted to hospital from home and are expected to be discharged home. We will exclude older adults who prior to the fracture were: unable to walk 10 meters; diagnosed with dementia and/or significant comorbidities that would preclude their participation in the clinical service.

Eligible participants will be randomly assigned to the Intervention or Usual Care groups by remote allocation. Treatment allocation will be concealed; investigators, measurement team and primary data analysts will be blinded to group allocation. Our primary outcome is mobility, operationalized as the Short Physical Performance Battery at 12 months. Secondary outcomes include frailty, rehospitalizations, falls risk factors, quality of life, as well as physical activity and sedentary behaviour. We will conduct an economic evaluation to determine health related costs in the first year, and a process evaluation to ascertain the acceptance of the program by older adults, as well as clinicians and staff within the clinic.

**Trial registration number:**

ClinicalTrials.gov: NCT01254942

## Background

Hip fractures are serious, life-limiting and costly events for older adults. Each year in Canada there are over 27,000 hip fractures [1], and older adults who sustain a low-trauma hip fracture have higher risk of death and disability. In the first year after the fracture, as many as 20% of people die [2]; and up to half of seniors will not regain their pre-fracture level of mobility [3,4] leaving them at risk for further falls [5] and fracture injuries [6-9]. Therefore, despite advances in surgical and medical management following hip fracture, up to half of hip fracture patients do not regain their independence or return to prefracture functional mobility.

After hip fracture, systematic structured follow-up strategies for older adults [10,11] improve investigation rates for osteoporosis; and fracture liaison services [10-23] after fracture are beneficial. Many previous interventions, however, have focused on bone health management, and to our knowledge only a few studies [18,20] have included patient referral for falls risk assessment. Osteoporosis care can be improved, but as fractures occur because of low bone mass and *falls*, it is important to also address falls risk [24]. It is noteworthy that despite being prescribed osteoporosis medication [11] some patients who attended a fracture liaison service had a subsequent fall-related low trauma fracture. Hence, the need to coordinate both *falls prevention and bone health *initiatives [11].

Ferrucci and colleagues [25] discuss that hip fracture can result in "catastrophic disability" for older adults due to the unanticipated deterioration in functional ability [25] in some activities of daily living and mobility. Decreased mobility, in turn, impacts on the risk for future injury. Importantly, older adults who sustain hip fracture are at an increased risk of future hip fracture [26,27]. A systematic review [8] emphasized that previous falls [28], low bone density [28,29], and mobility impairment [28] are major risk factors for second hip fracture. Approximately 90% of fractures occur as a result of a fall [30] and after hip fracture, up to half of people can fall again within the first 6 months following fracture [5,31]. These data emphasise the importance of a two-pronged approach to reducing hip fractures - addressing falls risk as well as low bone mass [32].

Compelling evidence supports the recommendation for strength and balance exercises for falls risk reduction in vulnerable populations [33-36]. Exercise improves lower limb muscle strength and it can maintain bone mass in post-menopausal women [37-39]. A Cochrane systematic review [40] reported six trials that evaluated exercise interventions for people after hospital discharge following hip fracture. Balance and strength measures improved overall; in particular, Binder and colleagues [41] reported a significant improvement in mobility measures after a six month out-patient physical therapy intervention.

Therefore, the purpose of the current study is to evaluate the clinical and cost effectiveness of a novel post-discharge fracture management strategy for community-dwelling older adults after hip fracture. It is anticipated that initiating an individualized outpatient management program after hospital discharge, which includes falls and fracture risk assessment and management, and an individualized exercise program under the ongoing guidance of a physical therapist, will improve mobility, and reduce disability and falls.

## Methods/design

### Study Aims

The primary aim of this study is to assess the effectiveness of a comprehensive post-fracture clinic with extended rehabilitation for community-dwelling older adults following hip fracture on mobility. Secondary aims include prospectively (i) determining costs associated with hip fracture, and our intervention, and (ii) completing a process evaluation as part of our integrated knowledge translation plan.

### Study Design and Setting

We propose a parallel group, pragmatic [42] single blind randomized controlled trial of two different delivery modes of post hip fracture management- Usual Care alone versus Usual Care plus specialized outpatient fracture follow-up management. This study will take place at two academic teaching hospitals in Vancouver, Canada. Vancouver is the largest city in the province of British Columbia and with an estimated population of 578,000 and 13% of the population are adults aged 65 years+ (2006 Census Data; http://vancouver.ca/commsvcs/planning/census/2006/index.htm). Our clinic is located within the Vancouver Coastal Health Authority (VCHA) catchment area.

#### Ethical Approval

We have obtained ethical approval from the University of British Columbia (UBC) Clinical Research Ethics Board, Vancouver Coastal Health Research Institute Ethics Board, and Providence Health Ethics Board. All participants will provide written informed consent prior to participating in the study (Clinical Trials Registration NCT01254942).

#### Participants

We will include 130 community-dwelling older adults (women and men) aged 65 years+ who, with a recent history (within past 3 months) of hip fracture, were admitted to hospital from home and expected to be discharged home. We will exclude older adults who prior to the fracture were: unable to walk 10 meters; diagnosed with dementia; and/or with significant comorbidities that would preclude their participation in the clinical service.

#### Identification of Eligible Participants

Our recruitment coordinator will identify and enrol patients into the study prior to discharge from hospital, rehabilitation unit and/or from a discharge list of eligible older adults. Identification of potential participants will be facilitated by the clinical staff; in addition, recruitment posters will also be placed on the ward and on the Centre for Hip Health and Mobility website. The recruitment coordinator will provide written and verbal information to all eligible participants.

#### Randomization

Treatment allocation will be concealed; a statistician independent of the study will generate the allocation sequence using randomized blocks of varying size; we will stratify randomization by hospital site and sex. This list will be provided to a centralized, web-based randomization service. At the completion of the baseline assessment the study coordinator will use the online service to determine the next allocation. Investigators, the measurement team and data analysts will be blinded to group assignment throughout the trial (Flow Diagram in Figure 1).

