### Statistical Analysis

#### Sample Size

We plan to recruit 130 participants over an 18-month period. Allowing for 15% loss to follow-up we will have 110 evaluable participants at 12 months. We have chosen to power the study to detect fairly large effect sizes as the proposed intervention represents an intensive use of scarce resources (geriatrician, physical therapists) and would need to demonstrate large effects to be considered for adoption by health funders. *Justification for sample size*: Given the anticipated presence of ceiling and/or floor effects in the SPPB we will compare the two groups, without adjusting using a Wilcoxon-Mann-Whitney (WMW) test. The WMW test can be characterized by the WMW odds ratio, OR_wmw _= π/(1-π) where π = Pr (Y_1 _< Y_2_) + 0.5 Pr (Y_1 _= Y_2_). Note, if there is no difference between the groups, π = 0.5 or equivalently, OR_wmw _= 1.0. If the OR_wmw _is 2.0, the odds are 2:1 that Y_1 _is less than Y_2, _i.e. π = 2/3. With 55 evaluable participants/group we will have >80% power to detect ORs of 2.0 or greater assuming α = 0.05 (2-sided) [66].

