#### Primary analysis

All analyses will be intention-to-treat; there will be no interim analysis. SPPB at 12 months post randomization will be compared between the two groups using the Wilcoxon-Mann-Whitney test. Point and interval estimates for the difference in medians will be calculated.

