#### Secondary analyses

All secondary analyses will be for descriptive purposes only. Point and interval estimates of the effect of the intervention on LEM scores at 6 and 12 months will be determined using a linear mixed model. The baseline LEM score will be included in the model as a covariate. Analyses for frailty, TUG and activity patterns as measured by CHAMPS and accelerometry will follow that of LEM. Types of management received and adherence to prescribed therapies will be described separately for each group. Analyses will be conducted at 6 months for descriptive purposes only.

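### Randomisation is stratified by site and sex, but the primary Wilcoxon test ignores the strata: it stays valid and adequately powered, yet is conservative if those factors predict SPPB

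*Protocol article*

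**What the plan says.** Under Randomization, the article describes blocks of varying size and says "we will stratify randomization by hospital site and sex". Study Design and Setting gives the number of sites: "This study will take place at two academic teaching hospitals in Vancouver, Canada". Two sites by two sexes make four strata.

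Under Sample Size, the article expects ceiling or floor effects in the SPPB and concludes: "we will compare the two groups, without adjusting using a Wilcoxon-Mann-Whitney (WMW) test". Primary analysis confirms the test: "SPPB at 12 months post randomization will be compared between the two groups using the Wilcoxon-Mann-Whitney test". It then adds: "Point and interval estimates for the difference in medians will be calculated". Neither section mentions site or sex, and no reason is given for leaving them out.

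**The concern.** Permuted blocks within strata force the arms to be nearly balanced on site and sex, so differences between strata can hardly contribute to the difference between arms. The plain WMW test takes its null variance from the pooled ranks, as if allocation had been unrestricted, and that variance includes the between-stratum spread. If site or sex predicts SPPB, the reference distribution is too wide, p-values tend to be too large and some power is given away.

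The article's reason for the choice does not cover this. Expected ceiling or floor effects justify a rank test; they do not justify an unstratified one. The stratified form of the same test handles ties and bounded scores equally well.

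**Working it through.** **1. The article's own power figure.** Inputs from Sample Size: 55 evaluable per group (N = 110), OR_wmw = 2.0 so π = 2/3, two-sided α = 0.05. Noether's formula with equal arms (c = 0.5):

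power = Φ( √(12·c·(1−c)·N) · |π − 0.5| − 1.96 ) = Φ( √330 · 0.1667 − 1.96 ) = Φ(3.028 − 1.960) = Φ(1.068) = 85.7%.

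The same formula needs 95 evaluable in total for 80%, and 110/0.85 gives 130 after rounding up. The stated figures reproduce.

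**2. Size of the conservatism, by formula.** Let R² be the share of SPPB variance explained by the four strata. The article gives no value, so R² is an assumption shown over a range. If the design removes that share from the contrast but the test keeps it in the variance, the standard error is overstated by 1/√(1−R²). The true type I error is then about 2·[1 − Φ(1.96/√(1−R²))]:

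- R² = 5%: 1.96 × 1.026 = 2.011, giving 4.4%
- R² = 10%: 1.96 × 1.054 = 2.066, giving 3.9%
- R² = 20%: 1.96 × 1.118 = 2.191, giving 2.8%

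**3. Size by simulation.** Four set-ups were used, each with permuted blocks within site by sex. Two had 110 evaluable participants; two randomised 130 and applied 15% loss. The effect was OR_wmw = 2.0, equivalent to a normal shift of √2·Φ⁻¹(2/3) = 0.61 SD. Not every set-up covered every R². Ranges are across set-ups; the last column is the range of within-set-up differences (stratified minus plain).

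| R² (assumed) | Type I, plain WMW | Type I, van Elteren | Power, plain | Power, van Elteren | Power difference (points) |
|---|---|---|---|---|---|
| 0% | 4.6–5.3% | 4.6–5.1% | 86.1–86.8% | 85.6–86.1% | −1.1 to −0.4 |
| 5% | 4.3–5.0% | 4.4–5.3% | 86.1–88.0% | 86.4–88.4% | +0.3 to +0.4 |
| 10% | 3.7–4.3% | 4.7–5.2% | 87.2–88.6% | 88.8–89.8% | +1.2 to +1.7 |
| 15% | 3.4–3.8% | about 5% | 89.2% | 91.6–91.7% | +2.4 to +2.5 |
| 20% | 2.7–3.6% | 4.7–5.4% | 87.7–89.2% | 91.6–92.5% | +3.2 to +3.9 |

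Monte Carlo error is about 0.3 points for type I error and 0.5 points for power. Formula and simulation agree in direction and approximate size.

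**4. How strong the strata would have to be.** Assume, for scale only, 72% women and a 60/40 split between sites. For site and sex to explain 5% each, the gaps must be √(0.05/(0.72·0.28)) = 0.50 SD for sex and √(0.05/0.24) = 0.46 SD for site. If sex alone carried 10%, the gap would be √(0.10/0.2016) = 0.70 SD, which exceeds the 0.61 SD treatment effect.

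**The case against.** The strongest reply is that nothing here is invalid. The type I error stays at or below the nominal level apart from simulation noise, the power claim reproduces, and power stays above 80% in every setting examined. A 10% share requires sizeable site or sex differences, and the article gives no reason to expect a large contrast between two teaching hospitals in one city. With weak strata the stratified test gains nothing and may lose up to about one point of power. All of this stands, and it limits the point to forgone efficiency.

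It could also be said that an unseen analysis plan might stratify the test. That does not remove the point: the absence of adjustment is stated outright, and the primary analysis section names the plain test.

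Four stronger readings are tempting and are not supported:

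- **The benefit of stratification is lost.** Balance on site and sex is achieved by the allocation, whatever test follows. Only its recognition in the primary p-value is missing.
- **The mixed models are wrong.** For LEM the article says "The baseline LEM score will be included in the model as a covariate", and "Analyses for frailty, TUG and activity patterns as measured by CHAMPS and accelerometry will follow that of LEM". This names one covariate without excluding others, full covariate lists are commonly left to the analysis plan, and the secondary analyses are declared descriptive.
- **The planned interval for the difference in medians is too wide by a known amount.** The article does not say how that interval will be computed, and the simulations above did not examine it.
- **Baseline SPPB must enter the primary model.** That may be argued on other grounds; stratification by site and sex does not imply it.

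**Conclusion.** The primary test does not follow the randomisation: four strata are used to allocate and none to analyse, by explicit choice and without a reason that fits. The consequence is conservatism, with no inflation of false positives and no threat to the sample size. Its size depends entirely on how strongly site and sex predict 12-month SPPB, which the article does not report: negligible at 5% of variance or less, about 1 to 2 points of power at 10%, and about 3 to 4 points at 20%. This is a worthwhile improvement to the primary analysis; it is not a flaw that would invalidate the trial's result.

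**What to change.** In Sample Size and Primary analysis, replace the plain WMW test with the van Elteren (stratified Wilcoxon) test over the four site-by-sex strata. Because that test does not itself yield a difference in medians, name a matching stratified rank-based estimate and interval, for example a stratum-aligned Hodges-Lehmann shift or a stratified WMW odds ratio. The unstratified test can be kept as a sensitivity analysis.

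Site and sex may also be added to the descriptive mixed models for consistency; this is optional.

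The cost is wording, provided it is settled before unblinding. Both factors are known at randomisation, and with 110 evaluable the strata average 27.5 participants. Recruitment, data collection and sample size are unchanged. If site and sex turn out not to matter, the simulated price was 0.4 to 1.1 points of power, with at least 85.6% remaining.

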**Figure 1 F1:**
[figure not shown]
**Flow diagram of the phases of the B4 Clinic trial**.

#### Study Interventions

##### Usual Care (UC) group

Participants who are randomized to the UC Group will receive usual orthopaedic and rehabilitation post-operative treatment for the hip fracture. Participants in the UC Group will be offered the Fracture Follow-up Clinic at 12 months (please see below for description).

##### Intervention (B4) group

Participants who are randomized to this group will attend an enhanced post-fracture follow-up clinic for outpatient management of falls and fracture risk. The clinic has been designed based on the need to assess both falls risk factors and bone health. A geriatrician will lead the clinic and will provide post-fracture assessment and management. The clinical assessment will focus on four key areas to address secondary prevention of future injury by addressing key domains that contribute to fall and fracture risk, and include assessment of: balance, bone health, brain function and bladder function = B4 Clinic. Based on identified need during the geriatric assessment, participants may also be referred to additional health professionals such as occupational therapist, registered dietician, social worker etc.

In addition, while at the clinic, participants will also be assessed by a physiotherapist who will recommend an exercise program and, may recommend subsequent onsite outpatient physiotherapy visits. Participants will also receive a standardized home exercise program. Following discharge from outpatient physiotherapy, participants will also receive up to four additional telephone calls based on motivational interviewing [43], and we will use techniques to problem solve and facilitate goal setting around mobility and regular engagement in physical activity. If during these sessions, the participant identifies a mobility concern, she/he will be encouraged to follow-up with the B4 Clinic.

### Outcomes

#### Data Collection Protocol

Measurements will be conducted at the Centre for Hip Health and Mobility, Vancouver Coastal Heath Research Institute on the Vancouver General Hospital site or at a participant's home at baseline (3 months post-surgical repair), 6 and 12 months.

#### Primary Outcome

Our primary outcome for this trial is mobility as measured by the Short Physical Performance Battery (SPPB) at 12 months. This valid and reliable measure of mobility has been developed with older adults to assess balance and other key lower extremity functions [44]. The SPPB is composed of three separate tests that are timed and categorized depending on performance: the tests include standing balance, gait speed and sit to stand performance. The SPPB can predict future disability in older adults [45].

### Secondary Health Outcomes

#### Mobility Measures

We will use: (i) the Lower Extremity Measure Scale (LEM) [46], a valid and reliable self-report measure developed specifically for people after hip fracture to assess functional status and to distinguish clinically important change over time [46]; and (ii) the Timed Up and Go (TUG) Test [47] to assess basic mobility function related to transfers, balance and walking capacity. An objective measure of leg strength will be collected.

Falls will be measured by self-reported daily fall diaries, which will be completed and reported monthly to study investigators and followed up by an independent investigator. We will also use the QuickScreen to characterize components of falls risk. This 10 minute test measures key components of falls risk [48] including performance based measures (standing balance, coordination, vision, lower extremity sensation and sit-stands) and self-report information on previous falls and medications. We will assess falls-related self-efficacy by the Short-form Falls Efficacy Scale-International [49].

#### Frailty

We will collect information related to the participants' degree of frailty using two methods: the Clinical Frailty Scale [50], and a frailty index from Fried and colleagues derived from our study measures [51].

#### Patterns of Physical Activity and Sedentary Behaviour

Once a month we will ask participants to complete a Community Healthy Activities Model Program for Seniors (CHAMPS) questionnaire, a valid and reliable 7-day recall self-report tool [52]. We will also ask participants to wear an accelerometer at three time points (baseline, 6 and 12 months) to objectively measure physical activity and sedentary behaviour patterns.

#### Bone Health

We will record the number of best practice bone health options (i) offered and (ii) utilized by all participants, using a list generated from the 2010 Canadian clinical practice guidelines [53] for diagnosis and management of osteoporosis.

#### Cognitive Performance

We will assess global cognition with the Montreal Cognitive Assessment (MoCA) [54] and components of executive function using the Trail Making (Part B) [55] and Stroop Colour Word Tests [56].

#### Continence

Urge incontinence is a risk factor for falls [57,58], and will be ascertained via screening questions [59].

### Descriptive Data

#### Hospital Medical Chart Review

We will collect information regarding previous hospital admissions; participants' health status prior to the hip fracture and at discharge, any complications during hospitalization for the hip fracture repair and the number of inpatient visits by physical and occupational therapists and related information. We will also check for any falls that participants may have while in hospital. In addition, we will record assessments of the four research areas (balance, bone health, cognition and continence) and physical therapy management that occurs as part of the B4 Clinic.

